**Ensuring ambulatory care for moderately malnourished children**

All case of moderate acute malnutrition (70 %< W/H <80%) will enter in an ambulatory program emphasizing an appropriate child-centered counselling on feeding practice and care. Home visits will be made once a week to assess feeding practices and child specifics problems, and needs. Although following the main recommendations reported in table 3, the rehabilitation will be thus tailored to each case. Two important aspects will be stressed: frequency and energy density of meals. Means to improve these two aspects will be defined in accounting for the purchase power and the food accessibility of each family. Families will be encouraged to use local foods, e.g. add 5 ml of oil in the gruel ration and provide the child with snacks several times during the day. RTUF could be purchased at the health centre. The follow-up of the nutritional status will be made once a week in the health centre. During every visit the anthropometric measures will be taken (weight height, MUAC) to follow the evolution and the presence of other diseases will be assessed for providing adequate treatment.

A child will be confirmed cured when his/her W/H>80% and growth curve ascending for two consecutive weighing (2 consecutive weeks).

A particular attention will be paid to children not responding to the programme in order to adapt rapidly and adequately the management. Children who have not gained weight after two weeks of follow-up will be thoroughly examined to assess the presence of chronic pathologies (cardiac malformation, renal deficiency, HIV infection, pulmonary tuberculosis) and begin an adequate treatment, if possible. If a chronic pathology is ruled out, the family will be encouraged to use RTUF. Children who developed a medical complication and/or loose weight will be transferred to the hospital.

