## Population and sample size

This study concerns all the health workers in the primary health facilities of the Houndé district and the children from 0 to 24 months as well as their mother or caretakers. The intervention unit is the health center and the population living in its catchment area, i.e. health centers will be randomized.

For the evaluation as well of the efficiency as of the impact of this intervention, the statistical unit will be consisted the center of health and its population of cover. On the level of each statistical unit, three types of samples will be necessary in comparison with the study populations:

- Health workers

A random sample of one health worker will be made by center.

*Inclusion criteria*: Personnel of health having at least one year of activity in the center.

Caregivers

Insofar as several outcomes used to compare the two groups of mother, the principal outcome used to compare the two groups, will be the proportion of caregivers having a good score of Knowledge on adequate breastfeeding and complementary feeding practices.

Several hypothesis have been considered to estimate the sample size. The reference method for the sample size calculation is the paper of Hayes et al for cluster design; we used equation N°4 of this paper

C=number of pairs=6 in our case Km = intracluster correlation coefficient; in the case of paired groups, 0, 25 is used as conservatory value.

= proportion of caregivers with a good score of Knowledge in the control group

= proportion of caregivers with a good score of Knowledge in the intervention group

n=sample size by cluster

The value of C being known in our case, we deduced from this equation, the values of n, according to several assumptions on the rate of caregivers with good knowledge and practices on breastfeeding and complementary feeding and according to two levels of power 1-β=0,80 or 0,90. This is shown in the table below.

**Estimate of the number of caregivers** necessary to compare the two groups

| = 0,25 | α=0,05  1-β=0,80 | α=0,05  1-β=0,90 |
| --- | --- | --- |
|  | n=15 | n=50 |
|  | n=33 | n=95 |
|  | n=11 | 20 |

By taking a maximum power, a sample of 95 women per cluster will be necessary, which is 1140 women in total.

*Inclusion criteria*: all women of childbearing age having a child into care from 0 to 59 months and living in the health center catchment area for at least one year at the time of the survey.

Children from 0 to 24 months

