Taking into account the duration of the intervention a notable change on the child nutritional status could be measured at the level of wasting; which is relevant to measure in children 0 to 24 months. The primary outcome, to compare the two groups will be the proportion of wasted children that is to say the proportion of children with weight for height Z score ≤ -2. According to the baseline data, this proportion was 16.4 on average in the district. The same equation cited above was used to estimate the number of required children. We considered the hypothesis that, after the intervention, the proportion of wasted children would decrease from 16.4% to 10% in the intervention area. Considering two levels of power the numbers of required children is summarized in the table below.

Table IV: Estimate of the number of children necessary to compare the two groups

| = 0,25 | α=0,05  1-β=0,80 | α=0,05  1-β=0,90 |
| --- | --- | --- |
|  | n=180 | n=650 |

We also considered other values of:

| = 0,20 | α=0,05  1-β=0,80 | α=0,05  1-β=0,90 |
| --- | --- | --- |
|  | n=115 | n=200 |

| = 0,30 | α=0,05  1-β=0,80 | α=0,05  1-β=0,90 |
| --- | --- | --- |
|  | n=800 | n=5000 |

We finally kept our first hypothesis with = 0.25, 1-β = 0.80 which gives n = 180 (180 children per cluster).

I*nclusion criteria*: all children 0 to 24 months whose parents residing in the health center catchment area for at least one year at the time of the survey.

The selection of women and children will be in population and randomly. In contrast, the number of children required (180 by cluster) being greater than the number of women (95 per cluster), and to be more operational, we will choose to include in the study women of childbearing age with at least a child under 24 months. This will allow us to select our two populations at the same time.

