**The intervention component**

**The intervention impact on health facilities functioning, child health and nutrition status:**

*Primary outcomes:*

- Child weight and height at 6 and 12 months

-rate of acute malnutrition

*Secondary outcomes*:

-Health provider’s knowledge about nutrition counseling and practices

-Caretakers knowledge about basic nutrition counseling, and breastfeeding and complementary feeding practices

- Caretakers satisfaction with health care

-Implementation of recommended feeding practices

-Child dietary intake

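### Protocol sections 3.5 and 3.6 contradict each other on which outcome is primary, so the protocol does not settle which result decides the trial

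*Protocol*

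**What the plan says.** Section 3.5 (Population and sample size) says of the children: "The primary outcome, to compare the two groups will be the proportion of wasted children", defined by a weight-for-height Z score of -2 or less. The sample size rests on the hypothesis that "the proportion of wasted children would decrease from 16.4% to 10% in the intervention area", with alpha 0.05, 80% power and a between-cluster coefficient of 0.25. The size kept is 180 children per cluster.

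The same section says of the caregivers that "the principal outcome used to compare the two groups, will be the proportion of caregivers having a good score of Knowledge". That outcome has its own table at alpha 0.05 and leads to 95 women per cluster.

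Section 3.6 (Evaluation) has two bullets under primary outcomes: "Child weight and height at 6 and 12 months" and "rate of acute malnutrition". Its secondary list includes "Caretakers knowledge about basic nutrition counseling, and breastfeeding and complementary feeding practices".

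Section 3.7 (Data collection) schedules anthropometry at 3, 9 and 12 months. Section 5 (Data analysis) prescribes linear and logistic regression with mixed models for all analyses. It gives no order among the outcomes.

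**The concern.** Naming the primary outcome is the protocol's own task, and here two sections do it in ways that cannot both stand. One analyst following 3.5 would rest the conclusion on wasting alone. Another following 3.6 would also treat weight and height as primary. Each could cite the protocol, and they could reach different confirmatory conclusions from the same data.

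The two lists also differ in what supports them. Section 3.5 chooses wasting because a notable change in it could be measured within the duration of the intervention, and it gives an effect size and a sample size. Weight and height come with no hypothesised effect and no sample size. The second bullet in 3.6 has no definition, population or time point.

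At stake are the false-positive rate, if several results may each carry the claim, and the power for wasting, if alpha has to be shared.

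**Working it through.** **1. The outcomes side by side**

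| Outcome | Section 3.5 | Section 3.6 | Sample size given |
|---|---|---|---|
| Proportion of children 0-24 months with Z score ≤ -2 | primary | not named as such | yes, 180 per cluster |
| Rate of acute malnutrition | not mentioned | primary, undefined | only if it means the row above |
| Weight at 6 and 12 months | not mentioned | primary | no |
| Height at 6 and 12 months | not mentioned | primary | no |
| Caregiver knowledge | principal, for caregivers | secondary | yes, 95 per cluster |

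Even if the rate of acute malnutrition is taken to mean wasting, the conflicts over weight, height and caregiver knowledge remain.

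**2. The time points.** Section 3.6 wants measures at 6 and 12 months; section 3.7 has 3, 9 and 12. If months count from the training, no 6-month measurement is scheduled. If months in 3.6 mean the child's age, the two could be compatible, but the protocol does not say so.

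**3. The plan's own figure.** The equation is not legible in the text at hand. I assumed a common pair-matched form, c = a + (z_α + z_β)² [p0(1-p0)/n + p1(1-p1)/n + k²(p0² + p1²)]/(p0 - p1)², with c = 6, k = 0.25, p0 = 0.164, p1 = 0.10 and 80% power. For a = 2, 1, 0 it gives no solution, 749 and 275 two-sided, and 660, 226 and 136 one-sided. So n = 180 is not reproduced. This depends on the assumed formula and is a separate matter; nothing below uses it.

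**4. False-positive rate, if any one result sufficed.** Assume each test is two-sided at 0.05, unadjusted, and that one significant result counts as success. For m independent tests the chance of at least one false positive is 1 - 0.95^m:

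- m = 2 (the two printed bullets): 1 - 0.9025 = 9.75%
- m = 3 (weight, height, acute malnutrition, one test each): 1 - 0.857375 = 14.3%
- m = 5 (weight and height at each of two times, plus acute malnutrition): 1 - 0.773781 = 22.6%; the upper bound under any dependence is 5 × 0.05 = 25%

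The documents give no correlations. Simulating five normal test statistics with an assumed common correlation of 0.3, 0.5, 0.7 and 0.9 (1,000,000 draws) gives 20.9%, 18.3%, 14.8% and 10.2%.

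**5. Power, if alpha were shared equally.** Take a wasting test with a true 80% power at two-sided 0.05. Its power at 0.05/m is Φ(1.960 + 0.842 - z), where z is the 1 - 0.05/(2m) normal quantile.

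- m = 2: z = 2.241, power Φ(0.560) = 71.2%; information needed to restore 80%: (2.241 + 0.842)²/(1.960 + 0.842)² = 1.21 times
- m = 5: z = 2.576, power Φ(0.226) = 58.9%; information needed: (2.576 + 0.842)²/(1.960 + 0.842)² = 1.49 times

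For comparison, going from 80% to 90% power takes (1.960 + 1.282)²/(1.960 + 0.842)² = 1.34 times the information. The protocol's own table raises n from 180 to 650 per cluster for that step. With the six pairs fixed, a five-way split would need more than 650 by the same table.

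**The case against.** The strongest reply is that the protocol states no success rule, and that the handling of several primary outcomes is commonly left to a statistical analysis plan, which is not shown here. That stands. A reader might infer that the trial can claim success on any of five outcomes, with a 22.6% error rate. The documents do not support that. They leave the route open but do not grant it, and the rates in step 4 are conditional on a rule that appears nowhere.

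The count is also open. Section 3.6 prints two bullets, and five is an expansion by measure and time. Section 5 lets mixed models handle repeated measurements, so the two time points may enter one model per measure, which gives three tests. Independence is implausible for weight and height in the same children.

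A reader might also infer that the protocol offers rival definitions of the outcome, since section 3.3.4 says "All case of moderate acute malnutrition (70 %< W/H <80%) will enter in an ambulatory program" and section 3.3.3 uses a mid-upper-arm cut-off. These are criteria for entering a programme or for referral, not evaluation outcomes. The only definition in the outcome and sample-size text is the Z score, and the bullet in 3.6 may well mean that. The fair criticism is that 3.6 does not say so.

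None of this removes the conflict in naming. An analysis plan would have to choose between two protocol statements, and either choice would depart from one of them.

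**Conclusion.** The point holds as a contradiction within the protocol and needs correction. Wasting is the single primary child outcome in 3.5. Weight and height join an undefined rate of acute malnutrition in 3.6. Caregiver knowledge is principal and sized in one section and secondary in the next. The 6-month measures do not match the schedule in 3.7 unless months mean child age.

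The contradiction needs no assumption; it can be read from the two sections. Its size does need one. If any one unadjusted result at 0.05 were taken as success, the error rate under independence would lie between 9.75% and 22.6%, depending on the count. For five tests it would be about 18% at an assumed correlation of 0.5 and about 15% at 0.7. These figures show what the ambiguity could cost; they are not the trial's error rate.

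**What to change.** In section 3.6, name as the single primary child outcome the one sized in 3.5: the proportion with a weight-for-height Z score at or below -2 in the random population sample of children aged 0-24 months. Attach one time point already in the schedule, for example the 12-month assessment, and state whether months mean child age or time since training. Use this definition in place of the undefined rate, and move weight and height to secondary. The programme criteria for weight-for-height percentage and arm circumference need no change for this purpose.

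Give caregiver knowledge the same status in 3.5 and 3.6. Reconcile the 6-month measures with section 3.7.

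The cost is protocol wording only: the sample size and alpha stay as they are. The downside is that weight and height can no longer carry a confirmatory claim. If the sponsor wants to keep them primary, the protocol must say how alpha is shared or how the tests are ordered, and restate the power for wasting. An equal split would lower a true 80% to 71.2% over two tests or 58.9% over five.

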**- Household survey (representative sample of 2164 households including 3912 children).**

**Population of under five children in the district40.000**

**Malnutrition rates in the district:**

- 16.4 % of the under-5 children are wasted and 38.7% are stunted (35.7% are underweight)
- 39% of the children ages 0-59 months had been sick during the previous two weeks

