## Study design

The intervention will be evaluated by a pair-matched, cluster-randomized controlled trial . Health facilities, together with the population living in their catchment area, will be matched by pair on the basis of accessibility criteria (distance to the district hospital), functioning criteria (number and profile of health workers, measles vaccine coverage, attendance rates of the growth monitoring programme, utilization rates of health facilities) and population characteristics (households socioeconomic indicators, child morbidity, rates of child wasting and stunting). Scoring of all health facilities will be based on the baseline data, and such score will be used to pair health facilities. Within each pair, one health facility will be randomly allocated the intervention, the other one serving as a comparator.

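### The 16.4% control rate used to size the trial for children 0–24 months is the baseline rate for all under-fives; no 0–24-month rate is given

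*Protocol*

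**What the plan says.** Section 3.5 (Population and sample size) chooses wasting as the outcome for the child sample, "which is relevant to measure in children 0 to 24 months", and defines it as weight-for-height Z-score at or below −2. It then gives the baseline level of that outcome: "According to the baseline data, this proportion was 16.4 on average in the district". The planning hypothesis is that "the proportion of wasted children would decrease from 16.4% to 10% in the intervention area".

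The baseline assessment box in the Background (April–June 2008; household survey of 3912 children) reports the figure for a wider age range: "16.4 % of the under-5 children are wasted and 38.7% are stunted (35.7% are underweight". No rate for 0–24 months appears anywhere in the protocol.

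The other inputs in 3.5 are "C=number of pairs=6 in our case", alpha 0.05, and a km of which it says "in the case of paired groups, 0, 25 is used as conservatory value". Tables for km 0.20, 0.25 and 0.30 give 115, 180 and 800 children per cluster at 80% power. The plan keeps 180, with km 0.25 and 80% power.

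**The concern.** The control proportion enters the calculation three times: in the binomial variance, in the between-cluster variance (which scales with the square of the proportion) and, through the assumed effect, in the difference to be detected. If the rate at 0–24 months is not 16.4%, all three change.

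Age groups within 0–59 months need not share one wasting rate. The protocol builds its contact schedule on the idea that nutritional risk varies with age. The Objectives section uses about the same level (16%) for a third population, children who consult. One number thus serves all under-fives, children 0–24 months and consulting children, with no statement that the rates were found, or are assumed, to be equal.

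What is at stake is whether the stated power describes the children who will actually be measured.

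**Working it through.** **Inputs.** From 3.5: p0 = 0.164, p1 = 0.10, c = 6 pairs, n = 180 per cluster, km = 0.25, alpha 0.05, power 0.80. Assumed: a two-sided test, and the usual pair-matched coefficient-of-variation formula, because the cited equation cannot be read in the extracted text:

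c = 2 + (zα/2 + zβ)² × [p0(1−p0)/n + p1(1−p1)/n + km²(p0² + p1²)] / (p0 − p1)²

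Solved for power:

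power = Φ( √[ (c − 2)(p0 − p1)² / V ] − 1.96 ), where V is the square bracket above.

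**Step 1: the plan's own figure.**
- Binomial part of V: (0.164×0.836 + 0.10×0.90)/180 = 0.00126.
- Between-cluster part of V: 0.0625 × (0.0269 + 0.0100) = 0.00231.
- V = 0.00357.
- √(4 × 0.064² / 0.00357) = 2.14, and Φ(2.14 − 1.96) = **57%**, not 80%.

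For 80% power, V may not exceed 4 × 0.064² / 7.85 = 0.00209. The between-cluster part alone is 0.00231, so no number of children per cluster reaches 80%; km would have to be below 0.238.

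Other variants at km 0.25 and 80% power do not return 180 either:

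| Variant | Two-sided n | One-sided n |
|---|---|---|
| Pair-matched | none | 660 |
| Unmatched | 749 | 226 |
| No added small-sample term | 275 | 136 |

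Under the unmatched two-sided form, 180 children per cluster give 67% power. The pair-matched two-sided form returns 180 if p1 is about 8.35%, or if km is about 0.15. This discrepancy exists before the age group is considered.

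**Step 2: the age mismatch alone.** Keep n = 180, 6 pairs and km 0.25, and vary only the control rate. The range 12% to 20% is an assumption.

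| Control rate | Same relative reduction (39%) | Same 6.4-point drop |
|---|---|---|
| 12% | 12% → 7.3%: power 52% | 12% → 5.6%: power 82% |
| 16.4% | 16.4% → 10%: power 57% | 16.4% → 10%: power 57% |
| 20% | 20% → 12.2%: power 61% | 20% → 13.6%: power 43% |

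At a constant relative reduction, power moves by about 4 to 6 points around 57%. At a constant absolute drop it moves much more, and in the opposite direction. If the 10% endpoint is held fixed instead, power is about 31% at a control rate of 14% and about 85% at 20%.

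**Step 3: sensitivity to km, for scale.** With 16.4% versus 10% and n = 180, km of 0.15, 0.20, 0.25 and 0.30 gives power of 80%, 69%, 57% and 47%.

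**The case against.** The best defence is that 16.4% is the only wasting rate the protocol prints, that 0–24 months lies within 0–59 months, and that nothing in the text shows the younger rate to be different. The Background passage on the first 18 months concerns feeding habits and linear growth; it does not say that wasting is concentrated there. All of this is fair, and it is why neither the direction nor the size of the error can be claimed. It does not rescue the sentence in 3.5, which presents an under-five figure as the baseline value of a 0–24-month outcome.

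A reader might infer two stronger points. The documents support neither.

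- **That km is also taken from a wrong source.** Facilities are to be paired on "population characteristics (households socioeconomic indicators, child morbidity, rates of child wasting and stunting", so centre-level wasting looks available while km is set by convention. But 0.25 is declared as a conservative convention, 0.20 and 0.30 are tabulated beside it, and nothing shows it to be wrong. No centre-level rates or chosen pairs are printed, and the household survey is described only as representative. An estimate would also be very imprecise. If the 3912 children were spread evenly over 27 centres there would be about 145 each. If 40% were aged 0–24 months (both assumptions), that leaves about 58. The sampling coefficient of variation of one centre's rate is then √(0.836/(0.164×58)) ≈ 0.30, larger than the 0.25 to be estimated. In a simulation of six pairs with a true value of 0.25, the estimate net of sampling error was zero in about 25% of runs, with a 95% range of about 0 to 0.52.
- **That the age mismatch lowers power from 80% to 57%.** It does not. The 57% arises at the plan's own inputs.

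**Conclusion.** The point stands as a mis-attributed input: the control rate for the 0–24-month outcome is the under-five rate. Its effect on power is unknown. Over an assumed 12% to 20%, power runs from about 52% to 61% at a constant relative reduction, and from about 82% down to 43% at a constant 6.4-point drop. These figures rest on the pair-matched formula, two-sided 0.05, 6 pairs, 180 per cluster and km 0.25.

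The failure of 180 to follow from 16.4% versus 10% at km 0.25 is a separate defect. Correcting the age group would not repair it, so both must be settled in the same recalculation. The finding does not extend to the choice of km.

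**What to change.** 1. From the baseline household survey, compute the prevalence of weight-for-height Z ≤ −2 in children 0–24 months, with a confidence interval that allows for the survey design. Give it in 3.5 as the control rate, and label 16.4% as the under-five figure.
2. State whether the planned effect is a relative reduction, an absolute drop or a fixed 10% endpoint, since power responds very differently to each.
3. Print the formula and the sidedness of alpha, and restate the power of 180 children per cluster with 6 pairs. The same recalculation must resolve why the present inputs give about 57% rather than 80%.
4. Keep the km tables for 0.20, 0.25 and 0.30, recomputed. A within-pair estimate from the baseline survey may be shown beside them with its uncertainty, as a check and not as a replacement.

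The cost is a few hours' analysis of data already collected. The stated power may change, and the sponsor may then have to reconsider the sample size or the number of pairs.

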***Targets***

*Outcomes:*

- To reduce morbidity rate in under five children

- To reduce wasting rate in consulting children by 50% (from 16% to 8%)

- To reduce the annual incidence of severe malnutrition by 50%

- To reduce the cost of severe malnutrition care

-*Processes:*

- To improve communication and management skills of primary health workers, particularly in the domain of nutrition, by 100% (all mothers should be advised about exclusive breastfeeding and complementary feeding, instead of the current 24%; all sick children should have their weight and length/height measured at any consultation; all mothers of sick children should be asked and advised about feeding practices)

- To improve knowledge and feeding practices of caretakers by 50% (75% of the mothers will give the colostrums to the newborn; 60% of the mothers will practice exclusive breastfeeding)

- To manage cases of severe acute malnutrition in each health facilities

- To manage cases of severe acute malnutrition in line with international recommendations of good practice.

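### With the stated inputs (16.4% vs 10% wasted, 6 pairs, km = 0.25), 180 children per cluster gives about 57% power, not the 80% claimed

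*Protocol*

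**What the plan says.** All of this is in the Protocol.

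- Study design: "The intervention will be evaluated by a pair-matched, cluster-randomized controlled trial".
- Population and sample size, caregivers: the method is taken from a cited paper on cluster designs ("we used equation N°4 of this paper"), with "C=number of pairs=6 in our case Km = intracluster correlation coefficient; in the case of paired groups, 0, 25 is used as conservatory value".
- Population and sample size, children 0 to 24 months: "The same equation cited above was used to estimate the number of required children". The hypothesis is that "the proportion of wasted children would decrease from 16.4% to 10% in the intervention area".
- The three wasting tables give, for 80% and 90% power, n = 180 and 650 at 0.25, 115 and 200 at 0.20, and 800 and 5000 at 0.30.
- The choice made: "We finally kept our first hypothesis with = 0.25, 1-β = 0.80 which gives n = 180 (180 children per cluster".

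**The concern.** The plan states every input that drives the result: two proportions, the number of pairs, km, alpha and n. The claimed power can therefore be tested. With only 6 pairs and a km of 0.25, variation between centres takes up most of the available precision, and sampling more children per centre does nothing to reduce it. That makes 80% power for a difference of 6.4 percentage points look implausible.

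At stake is how a null result on wasting would be read. If the true power at the planning values is near 57%, the risk of missing the stated effect is about 43%, not 20%. The tables also suggest that sampling more children can buy 90% power, which under the usual formula it cannot.

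**Working it through.** **Inputs.** p0 = 0.164, p1 = 0.10, c = 6 pairs, km = 0.25, alpha = 0.05, n = 180 (all from Population and sample size). Two-sided testing is my assumption.

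**Formula (assumed standard matched-pair form).** c = a + (z_α/2 + z_β)² × V / (p0 − p1)², where V = [p0(1−p0) + p1(1−p1)]/n + km²(p0² + p1²). The added constant a is normally 2; I also tried 1 and 0.

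**Attempt to reproduce n = 180.** Solving for n:

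n = 0.227104 / [(6 − a)(0.064²)/7.849 − 0.0625 × 0.036896]

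Here 0.227104 = 0.137104 + 0.090, 7.849 = (1.960 + 0.842)², and the between-cluster term is 0.0625 × 0.036896 = 0.002306.

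- a = 2: 4 × 0.004096/7.849 = 0.002087, which is below 0.002306, so no n gives 80%.
- a = 1: 0.002609 − 0.002306 = 0.000303, so n = 749.
- a = 0: 0.003131 − 0.002306 = 0.000825, so n = 275.

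None of these is 180.

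**Power at n = 180.** V = 0.227104/180 + 0.002306 = 0.001262 + 0.002306 = 0.003568, and √V = 0.05973. Power = Φ(√(6 − a) × 0.064/0.05973 − 1.960).

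| Constant a | √(6−a) × 0.064/√V | Power |
|---|---|---|
| 2 | 2.143 | 57.3% |
| 1 | 2.396 | 66.9% |
| 0 | 2.625 | 74.7% |

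**Checks that need no constant.** A paired t-test on 6 pair differences (5 df, critical value 2.571, noncentrality 2.625) gives 56.1%. A beta-binomial simulation with 200,000 replicates gives 56 to 57%. Both support the a = 2 figure.

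**Ceiling.** As n grows without limit, a = 2 gives Φ(2 × 0.064/√0.002306 − 1.960) = Φ(0.706) = 76.0%.

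**The other cells (two-sided, 16.4% vs 10%).**

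| km, power | Printed n | a = 2 | a = 1 | a = 0 |
|---|---|---|---|---|
| 0.25, 90% | 650 | none | none | 6899 |
| 0.20, 80% | 115 | 371 | 200 | 137 |
| 0.20, 90% | 200 | 2722 | 480 | 263 |
| 0.30, 80% | 800 | none | none | none |
| 0.30, 90% | 5000 | none | none | none |

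At km = 0.30 the between-cluster term is 0.09 × 0.036896 = 0.003321. That exceeds even the a = 0 allowance of 0.003131, so no two-sided form reaches 80%.

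**The label on km.** Read literally as an intracluster correlation, 0.25 with n = 180 gives a design effect of 1 + 179 × 0.25 = 45.75. The 6 × 180 = 1080 children per arm would then count as 1080/45.75 ≈ 24. That cannot sit beside a table offering 80% power. In the formula, km acts as a coefficient of variation between clusters within pairs.

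**Effect the design can detect.** With a = 2 and n = 180, power reaches 80% when p1 is about 8.3%.

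**The case against.** **The equation is not visible.** The formula, the symbols for the proportions and the first column of the tables are missing from the text as read, and only alpha is given. So the exact 57% is an inference. This stands, and it is why I give a range. It does not rescue n = 180: every two-sided form at 6 pairs lies between 56% and 75%. A one-sided test with no constant does exceed 80% (83.6%), but it would call for n = 136, and the plan states no one-sided test. It also reaches 80% at km = 0.30 with n = 347, so the statement that no n suffices there is limited to two-sided forms.

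**km may be lower in truth.** The plan presents 0.25 as a cautious value, and pairs are matched on baseline wasting among other criteria. At km = 0.15 the same formula gives about 80% at n = 180. But the plan ties its 80% to km = 0.25, so the stated claim is still wrong. What stands is that 57% is the power at the planning value. A reader might infer that it is the trial's actual chance of success, and the document does not support that.

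**The tables may belong to another effect.** A reader might infer that they were computed for the target under Objectives, "To reduce wasting rate in consulting children by 50% (from 16% to 8". For 16% to 8% with a = 2 the required n is 165 and 477 at 0.25, 105 and 180 at 0.20, and 545 and none at 0.30. No printed cell matches. That target also concerns consulting children, whereas this sample is drawn at random from the population. The origin of the tables cannot be established.

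**Conclusion.** The point holds. For the wasting comparison the plan states a power that its own inputs do not give: about 57% at n = 180 instead of 80%, assuming a two-sided test and the standard matched-pair formula, and at most 75% if the small-sample constant is dropped. Under the standard form, more children per centre cannot close the gap. The tables for 0.20 and 0.30 are not reproduced under any of the two-sided forms, so this is more than a single misprint. The name given to km contradicts its use.

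The finding concerns wasting only. The Evaluation section also lists child weight and height at 6 and 12 months as primary outcomes, and nothing here bears on power for those. Nor does it follow that the trial must enlarge; what is wrong is the stated power.

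**What to change.** 1. Recompute the three wasting tables for 16.4% vs 10% with 6 pairs, and mark cells that no n can reach.
2. Print the formula, including any small-sample constant, and state whether alpha is one- or two-sided.
3. Replace the 80% claim with the power that the design has: about 57% at n = 180, 6 pairs and km = 0.25 under the standard two-sided form.
4. If wanted, add as a property of the design that 80% power corresponds to a fall from 16.4% to about 8.3%. Do not tie this to the target for consulting children.
5. Relabel km as the between-cluster coefficient of variation within matched pairs.

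The cost is a protocol wording change and a less favourable stated power. No further children or centres are required.
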